### Study visits and specimen collection

The first prenatal specimen collection ideally occurs prior to 13 weeks’ gestation. If a participant is recruited after 13 weeks’ gestation, then first prenatal collection occurs as soon after enrollment as possible. At this study visit, site coordinators collect prenatal urine and buccal samples from the primary participant. If the primary participant consents to recruitment of the other biological parent, then the study coordinator also will approach the other biological parent for written informed consent. If given, they will collect buccal and urine specimens from the secondary participant, if consented. The study coordinator will email links to participants to complete pre-conception, food frequency, and stress questionnaires electronically. Study personnel conduct prenatal/medical chart reviews and contact participants for follow-up if needed.

The second prenatal collection occurs at the first prenatal visit that is between 14- and 27-weeks’ gestation and at least 4 weeks after the first prenatal collection while the third prenatal collection occurs at the first prenatal visit that is after 28 weeks’ gestation and at least 4 weeks after the second prenatal collection, if practicable. Collection of a specimen outside the ideal time frame is preferred over not collecting a specimen. Study team members collect a urine sample from the primary participant and email the primary participant links to food frequency and stress questionnaires. If applicable and not yet collected, they attempt to collect buccal and urine samples from the other consented biological parent and complete the pre-conception questionnaires with both participants if not previously administered. They conduct prenatal/medical chart reviews and contact participant for follow-up if needed.

Following delivery, study team members collect infant buccal specimens. If not previously collected, they also collect a third trimester urine specimen from the primary participant. The buccal specimen may be collected during the postpartum hospital stay or during an obstetrical follow-up visit up to 12 weeks after delivery. Study coordinators conduct prenatal/delivery medical chart reviews and contact participants for follow-up if needed. We employ multiple approaches for subject retention and engagement, including using social media, email, text message, study updates, and other methods that may be site specific. Our coordinator teams meet biweekly to discuss recruitment and engagement and share best practices.

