### Study protocol

A common protocol and manual of operations have been developed covering all aspects of the study for utilization by all sites. Obstetric and newborn care are delivered according to local practices and standards at the individual clinical sites. Trained study personnel perform all study-related procedures. Training procedures and evaluation methods have been developed and are utilized under the supervision of the Study Principal Investigators, to ensure consistency between sites. Within each site, implementation of general study procedure training is the responsibility of the Site Principal Investigator and Study Coordinator for each site. Quality control checks (via re-abstraction) are performed for primary outcomes by site Principal Investigators on randomly selected charts with and without adverse outcomes.

Study visits typically coincide with regular obstetrical care visits. Attempts are made to collect one prenatal urine sample and one prenatal buccal sample at each pregnancy trimester to assess urinary concentration levels and epigenetic alterations that may be occurring throughout pregnancy. Pregnancy trimesters are defined as first trimester (through 13 weeks), second trimester (14–27 weeks), and third trimester (28–42 weeks). Biospecimen collection and questionnaire data collection are administered separately from obstetric and neonatal clinical care. Biospecimen collection timing was chosen to facilitate evaluation of longitudinal/trimester effect of associations between herbicide concentrations and outcomes. Study adherence is incentivized by compensation to participants for their time and effort. The amount and types of compensation are determined in advance and are consistent across all sites throughout the study.

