Descriptive statistics, including appropriate parametric and semiparametric methods, will be used for continuous, binary, ordinal, and polytomous variables to describe characteristics of the cohort, exposures, and outcomes. We will examine the concentration data for appropriateness of cutoff values (quartiles, quintiles, high/low, etc.) or use as a continuous variable. Examples of statistical modeling approaches that we intend to utilize include least-squares linear regression, which will be used to describe the unadjusted associations between continuous outcomes (e.g., length of gestation or birthweight) and longitudinal exposure variable; and logistic regression, which will be used to describe the unadjusted association between a dichotomous outcome (e.g., diagnosis of pre-eclampsia or gestational diabetes, presence of congenital anomaly) and longitudinal exposure variables. Multivariate models will also be fit using suitable stratification and modeling adjustments for confounding and assessments of effect modification to evaluate associations between each outcome and multiple longitudinal exposures using methods appropriate to the structure of the data and analyses [62]. We will begin with simple multiple logistic regression models but will adjust to other appropriate models based on the data. To evaluate for the presence of exposure misclassification, an exposure matrix variable utilizing both biomarker and geospatially derived exposure estimates will be modeled with respect to each outcome [63].

Confounding variables have been determined a priori based on prior studies. Potential confounding factors to be considered are maternal age [64, 65], country of birth [66, 67], race/ethnicity [68, 69], height and preconception weight (including Body Mass Index) [70, 71], pregnancy weight gain [72, 73], marital status [64, 74], employment status [75, 76], socioeconomic status [77, 78], education level [78, 79], smoking status [80, 81], insurance coverage [82–84], alcohol use [85, 86], drug use, caffeine use [87], history of fetal loss and gestational age at loss [88], parity [89, 90], prenatal care [91], and rurality [92, 93]. As we will have residential address information, we will be able to explore the impact of location-based markers of social determinants of health such as distance to health care facilities, area deprivation, green space, and others.

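### Urine collected after delivery is called a third-trimester specimen, so third-trimester exposure can depend on gestational age at birth

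*Protocol article*

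**What the plan says.** All references are to the protocol article.

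- **Study visits and specimen collection, post-delivery paragraph.** It opens "Following delivery, study team members collect infant buccal specimens" and continues "If not previously collected, they also collect a third trimester urine specimen from the primary participant". No time limit is given for this urine. The limit that follows concerns the other specimen: "The buccal specimen may be collected during the postpartum hospital stay or during an obstetrical follow-up visit up to 12 weeks after delivery".
- **Same section, prenatal paragraph.** The third collection is at the first visit after 28 weeks and "at least 4 weeks after the second prenatal collection, if practicable". A general rule is added: "Collection of a specimen outside the ideal time frame is preferred over not collecting a specimen".
- **Study protocol.** "Attempts are made to collect one prenatal urine sample and one prenatal buccal sample at each pregnancy trimester". The third trimester is defined as weeks 28 to 42.
- **Table 3.** Urine is marked in the three prenatal columns only. Buccal sampling is also marked at the delivery and post-delivery visits. The footnote allowing later completion covers questionnaires, not urine.
- **Outcomes.** Gestational age at birth is primary. Preterm birth runs from 22+0 to 36+6 weeks.

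**The concern.** A urine sample taken after birth cannot represent exposure in weeks 28–42 of the pregnancy that has just ended. The need for it is also not random with respect to the primary outcome. A woman who delivers before her third prenatal visit can supply the specimen only afterwards, whereas a woman who delivers at term has usually had many weeks in which to give it.

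Suppose these specimens enter the analysis as third-trimester exposure and concentration differs after birth, for example through diet, fluids or hospital stay. An association with gestational age then appears without any herbicide effect. It can run either way: higher postpartum concentration would make the herbicide look harmful, and lower concentration would make it look protective. Adjusting for maternal covariates does not remove it, because the cause is the date of sampling relative to delivery.

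The study claims to detect an exposure R² of only 0.003, so a small artefact is not obviously negligible.

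**Working it through.** **1. The passages side by side.** The trimester definition and the sampling aim make the third urine prenatal. Table 3 agrees. The post-delivery paragraph does not: it collects the missing specimen after birth and keeps the third-trimester name. The off-window preference encourages collection but does not say how such a specimen is labelled.

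**2. Who needs the catch-up specimen.** If the second collection is at 27 weeks, the third falls at 27 + 4 = 31 weeks or later. Births at 22–27 weeks have no third trimester at all. Births from 28 to about 31 weeks may precede the visit. Later births need the catch-up only if the visit was missed for another reason.

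**3. The plan's own figure, used only as a scale.** For one added predictor (5 covariates with R² 0.20, alpha 0.05, power 80%), solve the noncentral F test with noncentrality N·f² and 1 and N−7 degrees of freedom; then R² = f²(1−0.20)/(1+f²). At N = 1,800, f² ≈ (1.96+0.84)²/1,800 ≈ 0.0044, so R² ≈ 0.0035. At N = 2,000 it is 0.0031. The stated 0.003 is reproduced to the digit given. With an assumed gestational-age SD of 1.8 weeks, the detectable slope at 1,800 is √0.00348 × 1.8 = 0.106 weeks per SD. At 1,600, which is what 20% loss from 2,000 leaves, R² is 0.0039 and the slope is 0.11.

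**4. Illustration with modest assumptions.** None of these is in the article except the 10% preterm (180/1,800): no true effect, third sample planned uniformly over 28–33 weeks, 3% otherwise missed, SD 1.8 weeks. By simulation, 9.1% of preterm and 3.0% of term specimens are then post-delivery.

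| Shift after birth (SD) | Spurious slope (weeks per SD, absolute) | Share of 0.106 |
|---|---|---|
| 0.25 | 0.018 | 17% |
| 0.50 | 0.033 | 31% |
| 0.75 | 0.047 | 44% |

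Against the slope at 1,600 the range is 16–42%. A repeat run with a left-skewed gestational-age distribution gave about 0.015, 0.029 and 0.045. With a normal distribution almost no births precede 33 weeks and the bias vanishes, so the result depends on the early-preterm tail. With a standard error near 1.8/√1,800 = 0.042, slopes of 0.018 and 0.047 lie about 0.4 and 1.1 standard errors from zero. The two-sided 5% test would then reject about 7% and 20% of the time.

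**5. Illustration with larger differences.** N = 1,800, 10% preterm, no true effect, 1,000 runs per setting, unadjusted regression on third-trimester concentration. The shares are assumed.

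| Post-delivery share, preterm vs term | Shift 0.25 SD | 0.5 SD | 1.0 SD |
|---|---|---|---|
| 30% vs 5% | 11% | 26% | 67% |
| 50% vs 10% | 18% | 50% | 96% |
| 50% vs 5% | 20% | 64% | 99% |
| 20% vs 20% | 5% | 4% | 5% |

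Entries are false-positive rates. With no shift they are 4.5–5.5%. A shift of −0.5 SD gives nearly the same rates as +0.5 SD (25% at 30% vs 5%). The row with equal shares shows that the cause is differential timing, not postpartum sampling as such.

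**The case against.** **The article does not say that the specimen enters a third-trimester exposure metric.** It names a catch-up collection. The Statistical analysis section offers examples of approaches, and the classing of off-window samples is ordinary analysis-plan content. This stands in part. How the specimen is analysed is not stated, so the bias is conditional. The name is stated, however, and it contradicts the article's own definition and Table 3.

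**The size is assumed.** This stands. Neither the post-delivery share nor the concentration shift is in the article. The high rates in step 5 come from shares of 30–50% in preterm births, against 9% in step 4, so they do not corroborate the smaller illustration. First- and second-trimester urine is largely unaffected for gestational age.

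**Excluding the specimens creates missing data related to the outcome.** This also stands, and the fix must deal with it.

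Stronger readings that a reader might infer are not supported:

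- *That reverse causation cannot be told apart from a herbicide effect for gestational diabetes and hypertension.* The article plans "logistic regression, which will be used to describe the unadjusted association between a dichotomous outcome" and longitudinal exposure, without stating that the sample must precede the diagnosis. Such a rule is commonly left to the analysis plan. Enrollment is by 20+6 weeks and gestational hypertension counts only after 20 weeks, so the first urine generally precedes it.
- *That urine after organ formation is a consequence of an anomaly.* That is a question of the relevant exposure window. Limiting anomaly analyses to first-trimester samples would drop eligible women recruited after 13 weeks from an analysis expecting only 54 cases.
- *That urine may be taken up to 12 weeks postpartum.* That limit is given for the buccal specimen only.

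**Conclusion.** The contradiction is certain: a specimen collected after delivery is called third trimester, against the article's own trimester definition, its prenatal sampling aim and its schedule table. It is also clear from the visit timing that early births need this specimen more often. If it is used as third-trimester exposure, exposure measurement depends on the primary outcome.

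The size is not known. It requires a change in concentration after birth and a higher post-delivery share among early births. Under the modest assumptions the spurious slope is below half of the detectable one. It reaches the detectable size only with much larger differences in share or shift. The effect is confined to analyses that use the third-trimester sample. This should be corrected before exposure data are analysed. It does not undermine the cohort or its earlier-trimester analyses.

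**What to change.** 1. Reconcile the post-delivery paragraph with the trimester definition and Table 3. If post-delivery urine is still wanted, add it to the table under its own name and state its window.
2. Record the collection date relative to delivery for every urine. The article's list of study variables does not mention it.
3. Code any post-delivery urine as a separate postpartum time point and keep it out of prenatal exposure metrics in the primary analysis. Report an all-samples version as a sensitivity analysis.
4. Limit the third-trimester analysis to women still pregnant at sampling, for example as time to delivery counted from the sample date. Let first- and second-trimester urine cover the other women.

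The cost is mainly wording and coding, but there is a real downside: third-trimester exposure will be missing more often in early births. On the assumptions of step 4, about 0.091 × 180 ≈ 16 preterm and 0.030 × 1,620 ≈ 49 term births lose that sample, roughly 65 of 1,800 (3.6%). The third-trimester result then describes only pregnancies that continued to the sampling date and should be reported as such.

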### Exposure assessment

Coded urine and buccal samples collected at clinical locations will be transported to study site laboratories for processing per laboratory processing protocols and aliquoted into cryovials (as appropriate) and stored. Buccal and urine samples will be stored locally at ≤ -20 °C until they are shipped to the Indiana Bioservices biorepository in Indianapolis, Indiana, where they will be stored ≤ -70 °C. Samples will be batch shipped from Indiana Bioservices to an external analytic laboratory for completion of relevant assays. Details of the analytic methods utilized for biochemical concentration will be detailed in other manuscripts.

This study will utilize Geographical Information Systems and remote sensing data to develop herbicide exposure index estimates to complement biomonitoring results. An herbicide exposure index will be calculated using a buffer zone around a consenting participant’s residence. Using methods described in GIS-based exposure studies [46, 47], ArcGIS (ESRI Inc. Version 10.6.1) will be used to calculate the total land area within each the buffer zone for each crop type, which will be compiled based on USDA crop land use data [48]. The total area of each crop will be then multiplied by an average pesticide application rate estimated from data available from the USDA Chemical Use Program [49]. The total area of crop use land in each participant buffer zone (in km^2^) will be multiplied by the amount of pesticide application rate (in kg/km^2^) for each crop in order to estimate the total volume (in kg) of each pesticide applied within the buffer zone. An exposure index will be calculated for each pesticide expected to have been used. In addition, an aggregate exposure index will also be estimated. Herbicide exposure metrics will be utilized as an adjunct to biomarker analysis to evaluate relationships between geographic exposure and biomarker levels, as well as to refine associations between aggregate exposure and health outcomes.

### Outcomes

Study hypotheses relate to maternal and fetal reproductive outcomes that have been previously found to be associated with herbicide concentrations during pregnancy in human or animal studies. The primary outcome of the Heartland Study is gestational age at birth. Key human and animal studies supporting these hypotheses have been detailed in Tables 1 and 2. Maternal outcomes that will be considered are pregnancy loss, preterm birth, hypertensive disorders of pregnancy, and gestational diabetes. For purposes of the study, miscarriage is defined as the delivery of a liveborn fetus or a fetus who experienced fetal death for any cause before 20 + 0 weeks’ gestation. A miscarriage is considered early if delivery occurs at < 14 + 0 weeks and late if it occurs at ≥ 14 + 0 weeks’ gestation. Stillbirth is defined as fetal death before delivery after 20 weeks’ gestation [50]. Preterm birth is defined as delivery of a liveborn or stillborn infant for any reason between 22 + 0 and 36 + 6 weeks’ gestation [51]. Spontaneous preterm birth is defined as delivery that occurs after spontaneous onset of preterm labor or premature rupture of the membranes (PROM) or fetal membrane prolapse. Preterm labor is defined as spontaneous uterine contractions before membrane rupture, documented cervical change of at least 1 cm dilation or effacement during the admission, or dilation > 2 cm or effacement > 80% on admission for contractions. PROM is defined as spontaneous rupture of the membranes before the onset of contractions, regardless of subsequent labor augmentation or cesarean delivery. Indicated preterm birth is defined as delivery after induction or cesarean delivery between 20 + 0 and 36 + 6 weeks’ gestation for obstetric, maternal, or fetal indications. The indication for the delivery will be recorded. A birth is considered spontaneous unless documented otherwise. Term birth is defined as delivery of a liveborn or stillborn infant for any reason at ≥ 37 + 0 weeks’ gestation.

Hypertensive disorders of pregnancy include gestational hypertension, preeclampsia, eclampsia, and HELLP [hemolysis, elevated liver enzymes, and low platelet count] syndrome [52]. Gestational hypertension is defined as systolic blood pressure over 140 mmHg or diastolic blood pressure over 90 mmHg measured on at least two occasions 4 or more hours apart after 20 weeks’ gestation in a pregnant person that previously had normal blood pressure. Pre-eclampsia is gestational hypertension with proteinuria (300 mg or more in a 24-h urine collection, or other relevant clinical measurement). HELLP Syndrome and eclampsia are severe features of pre-eclampsia. HELLP Syndrome includes symptoms of Hemolysis, Elevated Liver Enzymes, and Low Platelet Count. Eclampsia is the manifestation of neurologic symptoms precipitated by hypertension. Diagnoses of these conditions made by a provider based on other clinical indications are also included.

Gestational diabetes is defined as a fasting plasma glucose ≥ 7.0 mmol/l (126 mg/ dl), a 2-h plasma glucose ≥ 11.1 mmol/l (200 mg/dl) following a 75 g oral glucose load, or a random plasma glucose ≥ 11.1 mmol/l (200 mg/ dl) in the presence of diabetes symptoms [53]. Additionally, gestational diabetes may be diagnosed clinically based on sequential screening with an abnormal 1 h glucose challenge test (50 g) followed by two abnormal values on a fasting 3-h glucose tolerance test, using appropriate cutoffs recommended by the American College of Obstetrics and Gynecology [54]. A participant is considered to have gestational diabetes if the criteria are documented or if a physician diagnosis of gestational diabetes is documented in the chart.

Primary fetal/newborn outcomes being evaluated are miscarriage, stillbirth, congenital anomalies/ malformations, fetal growth restriction, length of gestation, and birthweight. Secondary analyses may be performed to evaluate neonatal health status, including presence of respiratory distress syndrome, respiratory/ventilatory support, neonatal sepsis (confirmed/suspected, early/late onset), intraventricular hemorrhage, and infant discharge status. We are collecting buccal swabs which will be banked and plan to explore epigenetic changes associated with herbicide concentrations as well. We will plan the future epigenetic analyses based on techniques and methylated regions of interest that are cutting-edge and relevant at the time of those analyses. Specific plans for that future work are beyond the scope of this methods paper. The specific methods and hypotheses relating to the epigenetic analyses in the future will be detailed in papers arising from those analyses.

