### Design of the heartland study

The Heartland Study is occurring in multiple phases. Phase 1 evaluates associations between herbicide biomarkers of exposure and pregnancy and childbirth outcomes, as well as maternal and infant epigenetic changes. Phase 2 evaluates associations between biomarkers of herbicide concentration during intrauterine development and early childhood developmental outcomes, with a focus on neurological outcomes. This report details the methods and measurements of Phase 1. The study is registered on clinical trials.gov (NCT05492708).

In Phase 1, it is hypothesized that increased use of herbicides as measured from agricultural use data will correspond with herbicide biomarker concentrations collected during pregnancy; that herbicide detections/concentrations will be associated with adverse pregnancy and childbirth health outcomes, including gestational hypertension/pre-eclampsia, gestational diabetes, spontaneous abortion/stillbirth, congenital anomalies, shortened gestation, and low birth weight percentile; and that herbicide concentration will be associated with differences in epigenetic biomarkers.

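### Miscarriage and stillbirth are defined without regard to cause, so read literally they count induced terminations, although the Phase 1 hypothesis concerns spontaneous loss

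*Protocol article*

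**What the plan says.** All references are to the protocol article.

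- **Hypothesis (Design of the Heartland Study).** The Phase 1 outcomes include "gestational diabetes, spontaneous abortion/stillbirth, congenital anomalies, shortened gestation, and low birth weight percentile". The early-loss endpoint is named as spontaneous. The gestation endpoint is not limited in that way.
- **Miscarriage (Outcomes).** The rule takes in a liveborn delivery and also "a fetus who experienced fetal death for any cause before 20 + 0" weeks. It is early before 14+0 and late from then on.
- **Stillbirth (Outcomes).** "Stillbirth is defined as fetal death before delivery after 20 weeks". Cause is not mentioned.
- **Preterm birth (Outcomes).** "Preterm birth is defined as delivery of a liveborn or stillborn infant for any reason between 22 + 0 and 36 + 6" weeks. Spontaneous and indicated subtypes follow. For the latter, "Indicated preterm birth is defined as delivery after induction or cesarean delivery between 20 + 0 and 36 + 6" weeks. The section adds: "The indication for the delivery will be recorded". The default is: "A birth is considered spontaneous unless documented otherwise".
- **Role of the loss outcomes.** Miscarriage and stillbirth are listed among the primary fetal/newborn outcomes. Challenges and anticipated responses suggests that the two may be pooled as fetal death.

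Induced termination appears nowhere: not as an exclusion, a separate outcome or a censoring event.

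**The concern.** The hypothesis and the rule that scores it describe different events. The miscarriage rule expressly admits every cause of fetal death, and the stillbirth rule leaves cause open. Enrolment runs to 20+6 weeks and can begin in the first trimester, so a termination after enrolment is possible at any point these rules cover.

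If terminations are unrelated to herbicide exposure, counting them as losses dilutes a true association. If they are related to it through some non-biological route, they bias the association in a direction that cannot be predicted. Either way the damage is greatest where cases are few, and only 11 stillbirths are expected. Pooling stillbirth and miscarriage carries the problem into the pooled outcome. A termination for an anomaly would also tie the anomaly outcome to the loss outcomes by construction.

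**Working it through.** **Step 1: apply the rules as written.**

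| Event after enrolment | Rule met |
|---|---|
| Termination at 12 weeks | Early miscarriage |
| Termination at 18 weeks | Late miscarriage |
| Termination after 20 weeks, fetal death before delivery | Stillbirth |
| Termination after 20 weeks, liveborn | Not stillbirth |
| Termination delivered at 22+0 to 36+6 | Preterm birth; the indication is recorded |

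The first three rows put an induced event into a loss outcome, and no other sentence takes it out. In the last row the recorded indication allows the event to be found, although no rule uses it.

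**Step 2: possible weight among stillbirths.** The Statistical analysis section expects 11 stillbirths and 180 preterm births among 1,800 (11/1,800 = 0.6%; 180/1,800 = 10%). It gives no expected number of miscarriages, so no share can be computed for that outcome. It gives no termination rate either. Assume 0.1%, 0.25% or 0.5% of the 2,000 enrolled, that is n = 2, 5 or 10. The share of a case group is n/(n + expected cases).

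| n | n/(n + 11), stillbirth | n/(n + 180), preterm birth |
|---|---|---|
| 2 | 15% | 1% |
| 5 | 31% | 3% |
| 10 | 48% | 5% |

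The stillbirth column is an upper bound: it places every termination after 20 weeks with death before delivery. The preterm column likewise places every one at 22+0 or later.

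**Step 3: dilution.** If a share f of cases is unrelated to exposure, the log odds ratio shrinks to about (1 − f) × log OR. For a true OR of 1.5 per SD:

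- f = 10%: exp(0.9 × log 1.5) = 1.44
- f = 20%: exp(0.8 × log 1.5) = 1.38
- f = 30%: exp(0.7 × log 1.5) = 1.33

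**Step 4: gestational age at birth, the primary outcome.** Assume an SD of 2 weeks, 1,800 births, and terminations at about 22.5 weeks, 16.5 weeks below the mean. The base sum of squares is 1,800 × 2² = 7,200. Each such record adds 16.5² = 272.25 (the small shift in the mean is ignored). The variance ratio is 1 + k × 272.25/7,200. If the records are unrelated to exposure, the stated detectable R² of 0.003 is divided by this ratio.

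| k | Variance increase | R² of 0.003 becomes |
|---|---|---|
| 1 | 4% | 0.0029 |
| 2 | 8% | 0.0028 |
| 5 | 19% | 0.0025 |
| 10 | 38% | 0.0022 |

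The last two rows need 5 or 10 terminations clustered at 22–23 weeks, which nothing in the article suggests. One or two is the more cautious assumption.

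**The case against.** The best defence is that the article is condensed. It says that a common protocol and manual of operations cover all aspects of the study and that chart abstraction follows an operationalized protocol. A code for termination may exist there. One can also read the hypothesis and the miscarriage rule together, so that any cause means any medical cause of a natural death. This stands in part: we cannot say that abstractors do score terminations as miscarriages. It does not dispose of the point, because the published rule widens the definition in explicit terms and departs from the article's own hypothesis.

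Four stronger readings are tempting, and the document does not support them.

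- **That the preterm rule contradicts the hypothesis in the same way.** The hypothesis there is shortened gestation, subtypes are defined, and the indication is recorded. All-cause preterm birth with subtypes is a legitimate choice.
- **That every termination after 20 weeks becomes a stillbirth.** Only those with death before delivery do. Terminations at all gestational ages should therefore not be compared with the 11 expected stillbirths.
- **That the primary regression is badly distorted.** No sentence says that terminations receive a gestational-age value, and a large effect needs an unlikely cluster of records.
- **That rurality makes the bias exposure-linked.** The Background ties pesticide concentrations to residence near agricultural land and ties rurality to infant mortality. Rurality, insurance coverage and socioeconomic status are already listed as potential confounders, so adjustment may reduce bias from access. Adjustment does not correct an event that is misclassified.

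**Conclusion.** The point holds for miscarriage and stillbirth. It is clearest for miscarriage, where the all-cause wording is explicit and the hypothesis says spontaneous. For stillbirth it rests on the absence of any condition on cause and is limited to death before delivery. For preterm birth and gestational age it is a matter of stating how a recorded indication will be used.

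The size is unknown, because it depends on a termination rate that the article does not give. Under the assumed counts, even two misclassified events would be 15% of stillbirths at most. For gestational age, one or two records would add about 4–8% to the variance, given an SD of 2 weeks. The article already concedes low power for stillbirth, so the practical loss is mainly in interpretation: an association with loss, or with pooled fetal death, could not be read as one with spontaneous loss. The definition should be settled before outcomes are analysed.

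**What to change.** In the Outcomes section:

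1. Restrict miscarriage and stillbirth to spontaneous fetal death. If the liveborn limb of the miscarriage rule is kept, limit it to spontaneous delivery as well.
2. Record induced termination as its own category, not counted as a loss event and not included in any pooled fetal-death outcome.
3. For preterm birth and gestational age at birth, use the recorded indication to identify any termination at 22+0 weeks or later. Leave it out of the main analysis and add a sensitivity analysis that includes it.

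The sensitivity analysis matters because leaving out terminations for anomaly conditions on an event after exposure, and congenital anomalies are themselves a hypothesised outcome. Censoring at the termination date is not a ready alternative, since it has no direct meaning in the planned least-squares regression.

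The cost is one abstraction field, in charts that are already reviewed at every stage, and a few pregnancies leaving these analyses. If the manual of operations already has such a category, the change is only to the published wording.
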